**Group 4**	
CRC^f^	3.6

^*a*^*An extended version of this table, with colonoscopy result by FIT round, is shown in* Additional file 1*(Supplementary Table 2). In cases of multiple findings, participants are allocated to the most severe group. Numbers will therefore add up to 100%*

^*b*^*Polyps lost during colonoscopy or where the endoscopist considers biopsy unnescessary, for example hyperplastic polyps in the rectum*

^*c*^*Includes hyperplastic polyps with size < 10 mm and sessile serrated lesions without dysplasia and size < 10 mm*

^*d*^*Defined as any serrated lesions with size ≥ 10 mm or dysplasia*

^*e*^*Defined as any adenoma with either villous histology (≥25% villous components), high-grade dysplasia or polyp size greater than or equal to 10 mm* [52]

^*f*^*Defined as presence of adenocarcinoma arising from the colon or rectum. Collectively, advanced adenoma or CRC are referred to as advanced neoplasia* [52]

For the third aim, the outcome variable will be defined based on the metagenome data. We will monitor several aspects of the gut microbiome to describe the presence of bacterial strains and the functional potential in paired samples during re-establishment of the gut microbiome following bowel cleansing and colonoscopy.

Long-term effects in the study will be assessed 10 years after recruitment is completed. This will include an investigation of incidence and mortality of advanced colorectal lesions.

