### Statistical analyses and sample size considerations

The number of participants to include was chosen with the aim of providing adequate power for the development of a highly sensitive classification algorithm via data-driven analyses of gut metagenomes that will accurately identify FIT-positive individuals in need of clinical intervention.

The classifier will be trained using counts of taxonomic units, signature and genes categorized according to gene ontology or pathway membership from metagenomes, FFQ, demographic and lifestyle data as input variables, and advanced colorectal lesions as outcome (i.e. group group 3 and group 4, Table 2). The CRC risk classification will be done using machine learning algorithms suited to metagenome data, such as lasso regression [80], support-vector machines [81], random forests [82], multi-layer perception neural networks [83] and scalable tree boosting [84] algorithms. Evaluation of the classifier will be conducted in a leave-out test set. As outlined below, we believe that with sufficient sample size, development of a classifier with a sensitivity of 0.95 is achievable in the training set, being within the range of published reports [30, 33].

Interpretation of the classifier will be sought by post hoc analysis, quantifing the importance of individual features (taxa, genes and pathways) in making predictions. Stratified analyses will be done to evaluate the classifier within different subgroups of the population (e.g. by age group, sex and screening center).

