With a projected classifier sensitivity of 0.95 and a minimally acceptable sensitivity of 0.8, at 80% power and 95% confidence level, 50 participants with advanced colorectal lesions are required in the test set [85]. Classifier specificity in the setting of FIT-positive individuals will have a lower requirement, and we therefore set the expected classifier specificity to 0.75 and a minimally acceptable specificity of 0.6, thus requiring 100 participants with normal findings in the test set. Based on initial recruitment, we expect a participation rate of 58%, with 26% of participants having findings of advanced lesions or CRC (Table 2). By inviting 2700 FIT-positive BCSN participants, and splitting the training and test sets 80/20, a projected number of 1253 and 313 participants will constitute the training and test sets, respectively, which will include adequate numbers of participants with both advanced colorectal lesions and normal findings in the test set. With this sample size, we will also be able to perform stratified analyses. The machine learning analyses will be complemented by various multivariate regression analyses, stratified by the covariates outlined above.

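### The protocol says its sample size allows stratified analyses, but a test set with about 82 advanced lesions cannot meet the protocol's own case requirement in both halves of any two-way split of the classifier evaluation

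*Protocol article*

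**What the plan says.** Under *Statistical analyses and sample size considerations*, the protocol article takes Groups 3 and 4 combined as the classifier's outcome and says that the classifier will be evaluated in a leave-out test set. It then plans subgroup evaluation: "Stratified analyses will be done to evaluate the classifier within different subgroups of the population (e.g. by age group, sex and screening center").

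The next paragraph sets the size of the test set. For sensitivity the premise reads "With a projected classifier sensitivity of 0.95 and a minimally acceptable sensitivity of 0.8"; the error rates are given as "at 80% power and 95% confidence level"; and the conclusion drawn is that "50 participants with advanced colorectal lesions are required in the test set". For specificity the premise reads "we therefore set the expected classifier specificity to 0.75 and a minimally acceptable specificity of 0.6", and the resulting number is stated as "thus requiring 100 participants with normal findings in the test set". From 2700 invitations, 58% participation and an 80/20 split it projects 1253 people for training and 313 for testing, and calls the test-set numbers adequate. It then adds: "With this sample size, we will also be able to perform stratified analyses". A last sentence mentions complementary regression analyses, also stratified.

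No stratum count, precision or power is given.

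**The concern.** The adequacy statement closes a calculation that was made once, for the undivided test set. A reader will take it to cover the planned subgroup evaluation of the classifier. That evaluation can only use held-out people, because performance in the training set is not an honest estimate. The 313 are therefore the relevant base, and they have to be shared among the strata.

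Subgroup performance is part of the study's rationale: the Background notes that current screening performs worse in women and for right-sided tumors. Sex is one of the named strata. Tumor site is not, although *Outcome variables* says lesions may be subdivided by site. If stratum estimates are too imprecise, the study could neither show nor rule out a difference of the kind that motivates it.

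**Working it through.** **Inputs.** 2700 invited, 58% participation, 80/20 split, and the 50 and 100 requirements (sample-size section). From Table 2: Groups 3 and 4, 4.4 + 18.1 + 3.6 = 26.1%; Group 1, 11.2 + 2.4 + 18.2 = 31.8%; Group 2, 6.4 + 23.6 + 8.4 = 38.4%; CRC, 3.6%.

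**Reproducing the plan's figures.** 2700 × 0.58 = 1566; × 0.8 = 1253; × 0.2 = 313; 1566 × 0.261 = 409. All match the article.

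The 50 and 100 were checked as one-sample tests of a proportion against the minimum. Sidedness is not stated; 0.025 per side is used here. At 80% power, sensitivity needs 48 (exact) or 49 (continuity-corrected), close to 50. Specificity needs 78 (score formula), 85 (continuity-corrected) or 80–86 (exact), fewer than 100. At 50 and 100 the exact power is about 90% for each, so the requirement is on the generous side.

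**Contents of the test set.**
- Advanced lesions or CRC: 313 × 0.261 = 81.7, about 82
- Group 1: 313 × 0.318 = 99.5, about 100
- Groups 1 and 2: 313 × 0.702 = 219.7, about 220
- CRC: 313 × 0.036 = 11.3, about 11

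**The protocol's requirement applied per stratum.** Two strata need 2 × 50 = 100 advanced lesions. With 82, one stratum must hold 41 or fewer, however the split falls. Two strata of exactly 50 would need a test set of 100 / 0.261 = 383, or 383 / 0.2 ≈ 1,916 participants against 1,566. If normal means Group 1, 2 × 100 = 200 normals would need 200 / 0.318 = 629 in the test set, or about 3,145 participants.

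**Power per stratum, equal strata (an assumption).** Exact: find the smallest r with P(X ≥ r | n, p0) ≤ 0.025; power is P(X ≥ r | n, p1). Score: Φ{[(p1 − p0)√n − 1.96√(p0(1 − p0))] / √(p1(1 − p1))}.

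| Measure | n per stratum | Exact | Score |
|---|---|---|---|
| Sensitivity 0.95 vs 0.80, halves | 41 | 85% (r = 38) | 79% |
| same, one fewer | 40 | 68% (r = 38) | 78% |
| Sensitivity, thirds | 27 | 61% (r = 26) | 49% |
| Specificity 0.75 vs 0.60, halves, Group 1 | 50 | 51% (r = 38) | 59% |
| Specificity, thirds, Group 1 | 33 | 39% (r = 26) | 41% |
| Specificity, halves, Groups 1 and 2 | 110 | 90% (r = 77) | 92% |

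The jump between 40 and 41 is the saw-tooth of the exact test, so the fair statement for halves is about 68–85%. At one-sided 0.05, specificity with 50 Group 1 participants is 64% (exact) or 72% (score).

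**CRC alone (secondary).** If all 11 of 11 are detected, the 95% Clopper-Pearson lower limit is 0.025^(1/11) = 0.72, below the 0.80 minimum.

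**Robustness.** Table 2 includes 3.6% without colonoscopy, who are excluded. Rescaling by 1/0.964 gives about 85 advanced lesions and 12 cancers in 313. The conclusion is unchanged.

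**The case against.** The strongest reply is that the sentence claims feasibility only. It does not say that each stratum is powered for 0.95 against 0.80, and the 50 and 100 are stated for the whole test set; applying them per stratum is the reviewer's step. This stands. A reader might infer that the protocol contradicts itself, or that subgroup results will be presented as powered. The text supports neither. What remains is an unqualified adequacy statement placed directly after a calculation that does not extend to strata.

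Second, this sample size may refer to the full cohort, and the stratified regressions in the next sentence can use all 1,566 participants. That also stands for the regressions, which are not affected. It does not rescue stratified evaluation of the classifier, which the same section ties to the leave-out set.

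Third, the requirement exceeds what 80% power needs, so missing 50 or 100 is not the same as missing 80% power. On sensitivity, the measure the protocol puts first, two equal strata stay near the target. A reader might conclude that the test set cannot support any two-way split; the power figures do not bear that out.

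Fourth, the low specificity figures require normal findings to mean Group 1. The term is undefined. Since Groups 3 and 4 are the outcome, it could equally mean Groups 1 and 2; two equal halves then hold about 110 each and only the sensitivity side falls short of the requirement.

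Fifth, CRC alone is not among the named strata, so the 11 cancers break no stated promise.

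**Conclusion.** The concern holds as a statement about adequacy. The design does not deliver, per stratum of the classifier evaluation, what the protocol requires of one evaluation: about 82 advanced lesions cannot give 50 to each of two strata, equal or not. The arithmetic rests only on the article's own projections.

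The practical size depends on the split. It is modest for sensitivity in two equal strata. It is clear for three strata and grows with unequal splits or more strata, as screening center may bring. For specificity it is large under the Group 1 reading and absent for two equal halves under the Groups 1 and 2 reading. The power figures assume equal strata and 0.025 per side. The small number of cancers is a caution for any CRC-only result and does not carry the point. The overall evaluation in the undivided test set is not called into question here.

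**What to change.** Either of two changes would do.

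1. Keep the locked test set for the single overall claim. Report stratified performance (age group, sex, screening center, and lesion site or CRC if wanted) from out-of-fold predictions of nested cross-validation over all analysable participants, with confidence intervals. That base is about 409 advanced lesions, or about 204 per sex if split equally, and 1566 × 0.036 ≈ 56 cancers, before laboratory exclusions. Run it after the locked result is fixed so that the overall claim stays untouched. State that these estimates describe the modelling procedure and not the one locked model. The cost is computing time.

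2. Or restate the sentence: stratified test-set results are descriptive, are given with confidence intervals, and are not covered by the sample-size calculation. The cost is wording only.

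In both cases, say which groups count as normal findings. No change to recruitment is needed.

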## Discussion

CRC remains a major public health challenge with substantial personal and societal costs [22]. Screening is an effective measure to reduce disease burden [22]. However, current screening methods suffer from limitations, limiting the number of preventable cases. Innovative use of currently available methods represents a promising avenue for improvements in CRC prevention [22]. The current study is designed to contribute to the development of microbial biomarkers, using metagenome sequencing and comprehensive questionnaire and registry data for improved detection of advanced lesions and CRC in a FIT-positive population. The CRCbiome study is unique in that it uses data from the screening population to develop relevant biomarkers.

The idea of using microbial biomarkers to increase the performance of CRC screening has received increased attention with the adoption of high-throughput characterization of the gut microbiome. Ideally, combining microbial biomarkers with FIT testing could achieve the sensitivity of direct visualization methods and the uptake of non-invasive fecal tests. Several studies have demonstrated improved ability to discriminate individuals with healthy colons from those with advanced neoplasia when adding microbial biomarkers in the prediction model, more so for carcinoma (area under the curve (AUC) of 0.87–0.97 [30, 33, 34]) than adenoma (AUC of 0.76 [33]). Despite great promise, these studies have typically been limited by small sample sizes [30, 32–34], cross-sectional designs [30–34], use of suboptimal or low-resolution methods to study the gut-microbiome [30–33] and lack of data on important confounders [30–34]. The CRCbiome study seeks to address several of these shortcomings.

Major strengths of the CRCbiome study include its large sample size and prospective nature, use of state of the art methodology for studying the gut microbiome and access to detailed information on likely confounders of the relationship between the gut-microbiome and advanced colorectal lesions. A further strength of the study is in its organization and logistics structure, being nested within the BCSN. The immediate availability of clinically verified outcome data, via follow-up colonoscopies and cancer registry data, allow for prospective investigations on multiple outcomes relevant to the screening population (e.g. polyp recurrence). Access to comprehensive high-quality data on diet and lifestyle, including complete prescription histories, also enables the investigation of the predictive performance of more broad classifiers, laying the ground for personalized screening strategies, including risk-stratified approaches.

With a study population solely consisting of FIT positive participants, the projected number of individuals with high-risk lesions or CRC is relatively high (about 409 (26%), group 3 and 4, Table 2), thereby increasing the power to achieve accurate classification of advanced colorectal neoplasms. Still, whether findings in this population extends to cases missed by FIT testing is unknown.

Collection of follow-up samples at 2 and 12-months post colonoscopy represents an extension of the cross-sectional design of most prior studies, shedding light on the development of the gut microbiome following colonoscopy with or without removal of CRC precursor lesions. While there are examples of shifts in microbial profiles following colonoscopy, the gut microbiome typically reverts to the initial state within weeks [86]. Deviations from re-establishment of the gut microbiome both in the medium and long term have the potential for causal interpretations.

The study also has some limitations. Exclusive selection of FIT positive participants may limit the generalizability of the findings to those with bleeding neoplastic lesions. Consequently, improvements in diagnostic performance may be limited to specificity, and thus the ability to correctly classify healthy individuals. However, since lesions tend to bleed intermittently [87] and the study aims to identify potential causal pathways, we consider it likely that the identified biomarker also may have improved sensitivity in the screening population as a whole.

A further limitation is the lack of information on fecal metrics such as the Bristol stool scale, which has been shown to be an important determinant of microbiota richness and variance [88]. However, variation in microbiome profile due to stool consistency could likely be explored by use of gastrointestinal symptoms as a surrogate, data on which is available in the BCSN database.

Lastly, lack of follow-up data on diet and lifestyle may complicate the interpretation of microbial changes following colonoscopy. Even though prior studies in comparable study populations show that potential changes in diet and lifestyle following screening are modest [89, 90], caution in interpretation of follow-up samples is warranted.

The CRCbiome study represents a valuable source of data for further research. An example is access to complete prescription histories from the Norwegian Prescription Database that enables in-depth analyses of associations between a broad range of medications, microbial features and neoplasia risk, both during short and long-term follow-up. The fecal samples collected are also biobanked and can be used for other purposes beside the study aims of the current protocol. For instance, in addition to metagenome sequencing, the fecal samples can potentially be used for other omics analyses, such as transcriptome and metabolome analysis. All tissue specimens removed during colonoscopy are also available to the project, enabling in-depth molecular profiling.

The integration of a microbiome-based biomarker into national CRC screening programs is a long-term process, requiring many steps before enabling full implemtation. Ideally, the discovery phase will lead to the identification of a few selected features that will predict the occcurence of advanced colorectal lesions with high accuracy. These could then be combined by means of a biomarker panel for the development of a rapid test, which, following rigorous validation and testing, has the potential of being integrated into screening programs. The cost-effectivness of adding a microbial biomarker to the FIT test should be carefully evaluated before implementation.

## Conclusion

The CRCbiome study investigates the role of the gut microbiome, and its interactions with host factors, diet and lifestyle, in early stage colorectal carcinogenesis. Information obtained from this project will guide the development of a microbial biomarker for accurate detection of advanced colorectal lesions. By performing biomarker discovery within a screening population, the generalizability of the findings to future screening cohorts is likely to be high.

## Data Availability

Due to the principles and conditions set out in articles 6 [1] (e) and 9 [2] (j) of the General Data Protection Regulation (GDPR), research data generated in the CRCbiome study are not openly available. Further information on access to CRCbiome data can be found on the project web site [79]).

## Abbreviations

AICR: American Institute for Cancer Research
ATC: Anatomical Therapeutic Chemical
AUC: area under the curve
BCA: bovine serum albumin
BCSN: Bowel Cancer Screening in Norway
Bp: base pair
CRC: colorectal cancer
CRN: Cancer Registry of Norway
CT: computed tomography
DDD: defined daily doses
DNA: deoxyribonucleic acid
DPIA: Data Processing Impact Assessment
FFQ: food frequency questionnaire
FIMM: Institute for Molecular Medicine Finland
FIT: fecal immunochemical test
FU: follow-up
gFOBT: guaiac-based fecal occult blood test
ICD: International Classification of Diseases
KBS: Kostberegningssystem (“Dietary calculation system”)
KEGG: Kyoto Encyclopedia of Genes and Genomes
LDQ: lifestyle and demographic questionnaire
NCT: National Clinical Trial
NorPD: Norwegian Prescription Database
NSAIDs: non-steroid anti-inflammatory drugs
PCR: polymerase chain reaction
PBS: phosphate-buffered saline
SCFA: short chain fatty acid
STROBE: Strengthening the Reporting of Observational Studies in Epidemiology
WCRF: World Cancer Research Fund
WHO: World Health Organization
